#### **8.6 SAFETY OVERSIGHT**

Safety oversight will be under the direction of a DSMB composed of individuals with the appropriate expertise, including a Tanzanian clinician, clinicians with experience working on antiretroviral treatment or prevention projects and a biostatistician. The DSMB will meet every three months to assess safety and efficacy data on each arm of the study. The DSMB will operate under the rules of an approved charter that will be written and reviewed at the organizational meeting of the DSMB. At this time, each data element that the DSMB needs to assess will be clearly defined.

### **9. STATISTICAL CONSIDERATIONS**

#### **9.1 STATISTICAL AND ANALYTICAL PLANS**

A formal Statistical and Analysis Plan (SAP) will be developed prior to enrollment of any participants in this study.

## 9.2 STATISTICAL HYPOTHESES

**Primary endpoint 1:** We hypothesize that the proportion of eligible individuals who agree to initiate PrEP and are observed to take the first tablet on Day 0 will be higher in the workplace-based group than in the facility-based group. The null hypothesis is of no difference between the community- and facility-based groups; this will be a superiority comparison.

**Primary endpoint 2:** We hypothesize that the urine level of TDF in those enrolled in the workplace-based study group will be significantly higher than that in the facility-based group when measured at the 6-month post-initiation visit. The null hypothesis is of no difference between the community- and facility-based groups.

**Secondary endpoint 1a:** We hypothesize that the average number of refills made per initiated participant in the workplace-based group across the 6 months of study follow-up (i.e. at visits 2 and 3) will be higher than in the facility-based group. The null hypothesis is of no difference between the community- and facility-based groups; this will be a superiority comparison.

**Secondary endpoint 1b:** We hypothesize that the adherence per participant in the PrEP Champions intervention group across the 6 months of study follow-up (i.e. at visits 2 to 5) will be higher than that of participants in the national standard of care control group. The null hypothesis is of no difference between the two groups; this will be a superiority comparison.

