## **7. STUDY PROCEDURES AND SCHEDULE**

### **7.1 Study Procedures/Evaluations**

#### **7.1.1 STUDY SPECIFIC PROCEDURES**

- A medical history of each participant will be taken by clinicians at the sites. The history will include medication history including whether they are taking any over-the-counter medications. Based on this the Tanzanian healthcare provider will assess if they are taking any proscribed medications per WHO recommendations.

- A brief physical examination for vital signs, including height, weight and blood pressure will be completed by the clinical team.
- The clinical team will collect a finger-prick blood sample for point-of-care HIV and Hepatitis B surface antigen testing; , TDF testing for PrEP adherence, and will conduct a blood draw for laboratory-based serum creatinine, and syphilis testing.
- The results of all rapid tests will be provided to study participants at the time of testing. Serum creatinine tests will be discussed with participants if the results are abnormal.
- Standard HIV counselling will be provided to participants whether they test positive or negative, per national Tanzanian guidelines.

Adherence to emtricitabine/tenofovir disoproxil will be measured in three ways at each two-monthly visit. First, by self-reported adherence in terms of percentage of doses taken at the agreed time of day on the correct day. Second, by pill count of returned pills at the visit. Third, by a point-of-care urine assay for TDF. Patient-reported outcomes will be ascertained through a short questionnaire at each trial visit, in addition to the collection of baseline data prior to enrolment.

---

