### **7.3.2 ENROLLMENT/BASELINE**

#### **Baseline Visit (Visit 0, Month 0)**

- Obtain informed consent of potential participant verified by signature on study informed consent form.
- Verify inclusion/exclusion criteria.
- Division into the two study randomization groups 1 and 2
- Directly observe the first dose of emtricitabine/tenofovir disoproxil being taken and provide 28 (1 month) days of emtricitabine/tenofovir disoproxil.
- Counsel participant on adherence to emtricitabine/tenofovir disoproxil and need to contact the study if any changes in health arise.
- Conduct baseline questionnaire

---

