### **7.3.4 FINAL STUDY VISIT**

#### **Final Study Visit (Visit 6, Day 180 +/- 7; Month 6)**

- Record adverse events as reported by participant or observed by investigator.
- Record vital signs or other health conditions.
- Collect blood for creatinine and syphilis testing.
- A point-of-care Hepatitis B surface antigen (HBsAg)
- Collect urine for TDF testing for adherence

- Test for HIV
- Record participant's adherence to treatment regimen.
- Provide additional 28-days (1-month) supply of medication to the participant
- Provide final HIV prevention counselling to participant.
- Conduct endline questionnaire
- Inform of continued follow-up support to care by the national program
- Visit 6 will require between 1.5 and 2 hours to complete

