|----------------------------------------------------------|----------------------------------------|-------------------------|-------------------------|----------------------------|-------------------------|----------------------------|-------------------------|------------------------------------|
| TDF in urine                                             |                                        |                         |                         | X                          |                         |                            |                         | X                                  |
| Counsel on adherence                                     |                                        | X                       | X                       | X                          | X                       | X                          | X                       |                                    |
| Record adherence                                         |                                        |                         |                         | X                          |                         | X                          |                         | X                                  |
| Final HIV prevention counseling                          |                                        |                         |                         |                            |                         |                            |                         | X                                  |
| Information of follow up support by the national program |                                        |                         |                         |                            |                         |                            |                         | X                                  |
| Adverse event evaluation                                 |                                        |                         | X                       | X                          | X                       | X                          | X                       | X                                  |

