### 10.5.2 ANALYSIS OF THE PRIMARY EFFICACY ENDPOINT(S)

For **primary endpoint 1**, the proportion of eligible individuals who initiate PrEP will be measured based on observation of PrEP initiation at Visit 1. The initiation proportion secondary endpoint will be analysed as such using a two-sample test of proportion. The analysis set for this endpoint will be the ITT dataset including anyone who was screened, found to be eligible for PrEP and was randomized.

For **primary endpoint 2**, TDF level will be measured using urine-based TDF level estimation assay. TDF level will be analysed as a continuous measure in single nanograms per milliliter (ng/mL) and will be a single endpoint measure. The primary endpoint will be assessed using a two-sample t-test of log transformed data where the continuous outcome is TDF level and two exposure categories will be study group (workplace-based or facility-based PrEP). The analysis set for this endpoint will be the MITT dataset including anyone who initiated PrEP based on observed taking of their Day 0 pill.

For the test outcome, we will assume that women who default from treatment or are lost to follow-up will have TDF levels of zero.

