### 10.5.3 ANALYSIS OF THE SECONDARY ENDPOINT(S)

**Secondary endpoint 1:** The number of refills per initiated participant will be measured as the number of return visits (0-6) at which emtricitabine/tenofovir disoproxil was dispensed to the participant. The endpoint will be assessed twice, in both cases using one-way ANOVA. In the first instance, the likelihood of reporting 0,1,2,3,4,5 or 6 refills will be compared between the facility- and workplace-based groups; in the second instance, the likelihood will be compared between being or not being part of the omni-channel PrEP Champion intervention.

The analysis set for this endpoint will be the MITT dataset including anyone who initiated PrEP based on observed taking of their Day 0 pill.

The secondary analysis will involve no covariates; if preliminary analysis finds covariate imbalance, an ordered logistic regression model adjusting for imbalanced covariates will be run. The list of potential covariates that will be assessed will be specified in the SAP. Results will be presented as odds ratios with a 95% confidence interval.

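### Hypothesis 1b sets the PrEP Champion adherence comparison at visits 2 to 5, which under the protocol's own schedule includes two visits with no adherence record and omits the month-6 record

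*Protocol*

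**What the plan says.** All references are to the protocol; the SAP is not at hand.

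- **Section 9.2, endpoint 1b:** adherence per participant is compared between the Champion and standard-of-care groups "across the 6 months of study follow-up (i.e. at visits 2 to 5").
- **Section 3, secondary objective 1:** self-reported adherence is the effectiveness outcome for the Champion objective, because it covers the whole study period where the urine test sees only a short window. Hypothesis 1b does not itself name self-report; that is inferred from this section.
- **Section 7.3:** the numbering starts at "Baseline Visit (Visit 0, Month 0") and runs monthly to Visit 6 at day 180. The final visit includes the item "Record participant's adherence to treatment regimen".
- **Section 7.3.6:** the row "Record adherence" is marked at visits 2, 4 and 6 only. Visits 3 and 5 are refill visits with adherence counselling and a check on adverse effects.
- **Section 7.1.1:** adherence, self-report included, "will be measured in three ways at each two-monthly visit". Section 6.1.10 has self-reported use evaluated monthly as part of dose tracking.
- **Other visit labels in the statistical text:** endpoint 1a in 9.2 uses "across the 6 months of study follow-up (i.e. at visits 2 and 3"), yet 10.5.3 has refills "measured as the number of return visits (0-6"). Section 10.5.2 has initiation "measured based on observation of PrEP initiation at Visit 1".

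**The concern.** Hypothesis 1b equates the full six months with a specific list of visits, and the two do not agree under the schedule. A SAP or program that copies the list literally would look for adherence at two visits where none is scheduled and would leave out the month-6 record. Month 6 is the end of the period that self-report was chosen to cover. The complaint is not about detail left to the SAP: the protocol states a visit set, and its own schedule contradicts it.

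**Working it through.** **Step 1. Visits 2 to 5 against the collection text, 7.3 numbering (baseline = Visit 0).**

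| Source | Visits with self-report | In 1b's list and recorded | In 1b's list, not recorded | Recorded, but left out by 1b |
|---|---|---|---|---|
| 7.3, 7.3.6, 7.1.1 (two-monthly) | 2, 4, 6 | 2, 4 | 3, 5 | 6 |
| 6.1.10 (monthly) | 1 to 6 | 2, 3, 4, 5 | none | 1, 6 |

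The list matches neither source. Under the schedule of events, the last record used is at day 120 of 180.

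**Step 2. Other numberings.**

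- Initiation as Visit 1 (10.5.2), counted monthly: visits 2 to 5 are months 1 to 4, and month 6 is out.
- Initiation as Visit 1, counted two-monthly: months 2, 4 and 6 are visits 2, 3 and 4, and there is no visit 5.
- The five rows of the 7.2 test table as visits 1 to 5 (screening, then months 1, 2, 4 and 6): visits 2 to 5 are months 1, 2, 4 and 6. This ends at month 6. The protocol never states this numbering, it contradicts 7.3, and 7.3.6 has no adherence record at month 1.

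Endpoint 1a, in the same section, ends the same six months at visit 3. Both lists cannot end at month 6 under one numbering. This points to leftover labels rather than a decision to stop early.

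**Step 3. Records used, 7.3.6 schedule, full attendance.** 160 women × 2 = 320 of 160 × 3 = 480.

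**Step 4. Precision if the gap is constant.** The protocol does not say how visits are combined, so assume an unweighted mean of k visits with equal variances and a common between-visit correlation ρ. The variance of that mean is proportional to (1 + (k − 1)ρ)/k.

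| ρ (assumed) | k = 2 | k = 3 | Ratio |
|---|---|---|---|
| 0.3 | 0.650 | 0.533 | 1.219 |
| 0.5 | 0.750 | 0.667 | 1.125 |
| 0.7 | 0.850 | 0.800 | 1.062 |

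The planned 80 women per Champion group (40 + 40 in the 9.4.1 table) would carry the information of 80/1.219 ≈ 66 to 80/1.062 ≈ 75. If monthly self-reports were analysed instead (4 of 6 used), the ratios are 1.140 at ρ = 0.3 and 1.033 at ρ = 0.7.

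**Step 5. Estimate if the gap changes.** Let d2, d4 and d6 be the gaps at months 2, 4 and 6. Then

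(d2 + d4)/2 − (d2 + d4 + d6)/3 = (1/3) × [(d2 + d4)/2 − d6].

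The shift is zero if month 6 equals the average of months 2 and 4, negative if the gap is larger at month 6, and positive if it is smaller. The documents give no value for d2, d4 or d6.

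**The case against.** The best reply is that this is a labelling slip with a clear intent. Both 9.2 and section 3 say the whole period, the month-6 record is collected regardless, and a programmer would find visits 3 and 5 empty at once. One reading, the rows of the 7.2 table, even brings visits 2 to 5 out at month 6. All of that stands, and it keeps the point small. It does not make the stated list right: that numbering appears nowhere in the text and conflicts with 7.3, and the list is what a SAP would copy.

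Three stronger readings are tempting, and the documents support none of them.

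- A reader might infer that the month-6 self-report is dropped on every reading. It is under 7.3, but not under the 7.2-table reading.
- A reader might infer a definite bias or loss of power. Any such figure needs an assumed time course of the gap, an assumed standard deviation and correlation, and a mean-of-visits estimator. The protocol gives none of these.
- A reader might infer that monthly self-report in 6.1.10 must be cut back to agree with 7.1.1. Section 6.1.10 concerns dose tracking; the 1b list can be corrected without reducing that monitoring.

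It is also fair to say that self-report as the 1b outcome is an inference from section 3.

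**Conclusion.** The point holds as an inconsistency within the protocol. Under 7.3 and 7.3.6, the visit list in 1b includes two visits with no scheduled adherence record and leaves out one that has it, so two of three scheduled records would enter the comparison. A variance increase of about 6% to 22% with no change in the estimate applies if the gap is constant, and rests on the assumed correlations and the unweighted mean. With a gap that varies over time, only the direction of the shift can be stated. The 1b comparison is the one affected. The labels in 1a and 10.5.2 are related slips that should be corrected but change no result, since 10.5.3 counts refills over all return visits and both 9.2 and 10.5.2 tie initiation to the Day 0 pill. No primary endpoint result and no sample size depends on this.

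**What to change.** - **9.2, endpoint 1b:** replace the bracketed visit list with `(visits 2, 4 and 6; months 2, 4 and 6)` and state that self-reported adherence at these visits is the outcome.
- **9.2, endpoint 1a:** replace the bracketed list with `(visits 1 to 6)`, the return visits counted in 10.5.3.
- **10.5.2, primary endpoint 1:** change the visit label to `Visit 0 (Day 0)`.
- **6.1.10:** leave monthly dose tracking as it is.

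The month-6 record is already scheduled, so no visit, assay or participant is added. The cost is a wording amendment, which under 11.3 needs ethics review and approval. Section 9.1 has the SAP written before enrollment, and it should carry the corrected list.

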| 0.1                | 0.05                              | 0.605                              | 0.542 | 0.462 | 0.386 |
|                    | 0.10                              | 0.990                              | 0.978 | 0.949 | 0.897 |
|                    | 0.15                              | 1.000                              | 1.000 | 0.999 | 0.997 |
|                    | 0.20                              | 1.000                              | 1.000 | 1.000 | 1.000 |
| 0.2                | 0.05                              | 0.427                              | 0.378 | 0.321 | 0.269 |
|                    | 0.10                              | 0.937                              | 0.901 | 0.837 | 0.754 |
|                    | 0.15                              | 0.999                              | 0.998 | 0.992 | 0.976 |
|                    | 0.20                              | 1.000                              | 1.000 | 1.000 | 0.999 |
| 0.3                | 0.05                              | 0.357                              | 0.317 | 0.270 | 0.228 |
|                    | 0.10                              | 0.887                              | 0.839 | 0.763 | 0.675 |
|                    | 0.15                              | 0.997                              | 0.993 | 0.979 | 0.951 |
|                    | 0.20                              | 1.000                              | 1.000 | 1.000 | 0.998 |
| 0.4                | 0.05                              | 0.331                              | 0.294 | 0.251 | 0.213 |
|                    | 0.10                              | 0.860                              | 0.809 | 0.731 | 0.643 |
|                    | 0.15                              | 0.996                              | 0.989 | 0.972 | 0.938 |

|     |      |  |       |       |       |       |
|-----|------|--|-------|-------|-------|-------|
|     | 0.20 |  | 1.000 | 1.000 | 0.999 | 0.997 |
| 0.5 | 0.05 |  | 0.329 | 0.293 | 0.251 | 0.214 |
|     | 0.10 |  | 0.862 | 0.812 | 0.735 | 0.648 |
|     | 0.15 |  | 0.996 | 0.990 | 0.975 | 0.943 |
|     | 0.20 |  | 1.000 | 1.000 | 1.000 | 0.998 |

## 9.4 Measures to Minimize Bias

### 9.4.1 ENROLLMENT/ RANDOMIZATION/ MASKING PROCEDURES

The study will involve a cluster two sequential, independent randomized study. First, bars will be randomized at screening into either workplace-based or facility-based PrEP initiation and follow-up. Second, individuals will be concurrently randomized into either PrEP Champion intervention or no- PrEP Champion intervention for adherence and follow-up support. Anticipating that PrEP initiation will be approximately 10% in the facility-based arm vs. 25% in the workplace-based arm based on previously published studies in the region, we will randomize to either the facility-based arm or the workplace-based arm in a 2:5 ratio in order to obtain balance for ascertaining the second, more expensive outcome, 6-month adherence. If, as hypothesized, PrEP initiation is higher in the community- than the facility-based groups, our first primary outcome is powered to account for this unbalanced design. Under our primary hypothesized difference, in which 10% of those offered facility-based PrEP and 25% of those offered workplace-based PrEP join our study, the four study groups for our second primary outcome and secondary outcomes will look as in the table below:

|                                                               | Workplace-based
PrEP provision | Facility-based
PrEP provision |
|---------------------------------------------------------------|-----------------------------------|----------------------------------|
| Omni-channel PrEP Champion intervention
for PrEP adherence | 40                                | 40                               |
| National standard of care for PrEP adherence                  | 40                                | 40                               |

Individuals who discontinue the study early will not be replaced; since the primary endpoint is measured as urine level of TDF, they will automatically be assigned the value of zero. This non-replacement will not affect power, since by assigning discontinuing individuals a final outcome value no loss of sample size results.

The study will necessarily not be blinded. From the participants' side they will know which of the four study groups they are in based on the intervention they receive; from the investigators' side they will know who is receiving and not receiving workplace-based PrEP delivery and is part of an Omni-channel PrEP Champion intervention group.

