The study will involve two serial randomizations. The first randomization will occur at the bar level where barmaids working in a given bar will be offered the ability to initiate PrEP either: (1) at the bar in which the barmaid is working (“workplace-based”), and where they will be recruited to the study by Community based HIV care providers; or (2) at a selected public healthcare clinic already have trained health care workers trained on PrEP and already providing PrEP, as well as providing HIV treatment and care services (“facility-based”). The second randomization will be at the individual level where enrolled PrEP clients will be randomized to either: (A) being supported by an omni-channel PrEP Champion or (B) not being supported by an omni-channel PrEP Champion.

We will identify four facilities to participate in this PrEP provision trial. The criteria for selection will include: (i) existence of HIV care and treatment services; (ii) having a well-established ARV supply chain; (iii) having trained health care providers on how to offer PrEP; and (iv) provide HIV prevention services including condom distribution and comprehensive Positive Health Dignity Prevention (PHDP) services [24]. At each selected facility, we will identify a two well-trained HIV nurse counselors and one ART trained clinician, per WHO recommendations [26] and National PrEP Framework [25]. These staff will be paid for the overtime work they will undertake in supporting this study. The clinicians will be responsible for taking a clinical history and prescribing PrEP. The nurse counsellors will be responsible for providing adherence counselling, issuing PrEP pills and following-up clients for PrEP refills.

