## **Randomization 2: Omni-channel PrEP Champion**

We will randomly assign PrEP study participants into two groups. In the intervention group participants will be provided access to the support by an omni-channel PrEP Champion, to help participants adhere to their PrEP routine. Physical support will be provided through group or individual meetings when they come for PrEP refills whereas; virtual support will be via SMS, calls, WhatsApp groups or individual digital conversations. Additionally, clients will receive the national standard of care support, which includes reminders via SMS and phone calls through the health care provider. The PrEP Champions will regularly share informative standardized media including short, Kiswahili animated videos about PrEP use and adherence, essential PrEP messages, pictures, and gifs about PrEP. The media will be developed collaboratively with the National AIDS Control Program (NACP) staff and pre-tested before they are used in the trial. Participants will also be able to ask questions and discuss with and support each other. The WhatsApp messages and physical meetings will be moderated by the trained PrEP Champions. To share the digital information, the PrEP Champions will receive monthly internet bundles from the study team.

In the control group participants will receive the national standard of care, which includes refill reminders via SMS, phone calls and WhatsApp messages as done in the national standard of care. This randomization will be at the individual level. Those who are willing to participate will sign an additional consent form. Participants will be able to drop out at any time and feedback on the utility of the omni-channel PrEP Champions program will be solicited throughout the study. If a participant does not respond to the standard of care reminders and does not show up at her scheduled appointment, the study team will inform the facility or community PrEP lead about the non-responders for further follow up according to the national guidelines.

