### **4.3.3 EXPLORATORY ENDPOINTS**

1. Level of HIV-related knowledge, including PrEP
2. Characteristics of those accepting and declining to initiate PrEP
3. Proportion of those initiating PrEP retained in care at each study visit
4. Proportion of those initiating PrEP reporting >85% adherence at each study visit
5. Proportion of those initiating PrEP reporting side-effects
6. Number of HIV seroconversions at each study visit
7. Change in number of sexual partners reported in past 30 days from initiation to each study visit
8. Proportion of women reporting consistent condom use at baseline and final visit
9. Proportion of those initiating PrEP with STI symptoms at each study visit
10. Proportion of those initiating PrEP receiving a routine follow-up.
11. Proportion of those initiating PrEP declining being part of the omni-channel PrEP Champions intervention at baseline and at each study visit.
12. Proportion of those initiating PrEP with Tenofovir urine levels compatible with weekly dosing, dosing in the past 2 to 3 days, and dosing within the past 24 hours.

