### 7.3.6 SCHEDULE OF EVENTS TABLE

| Procedures                                                  | Recruitment and Screening Visit | Baseline Visit 0 | Visit 1 (refill) | Follow-up (Visit 2) | Visit 3 (refill) | Follow-up (Visit 4) | Visit 5 (refill) | Final Study Visit (Visit 6) |
|-------------------------------------------------------------|---------------------------------|------------------|------------------|---------------------|------------------|---------------------|------------------|-----------------------------|
| Selection of bars and recruitment of barmaids for screening | X                               |                  |                  |                     |                  |                     |                  |                             |
| Eligibility                                                 | X                               | X                |                  |                     |                  |                     |                  |                             |
| Screening/ Baseline/ Endline questionnaire                  | X                               | X                |                  |                     |                  |                     |                  | X                           |
| Informed consent                                            | X                               | X                |                  |                     |                  |                     |                  |                             |
| Demographics                                                | X                               |                  |                  |                     |                  |                     |                  |                             |
| Medical history                                             | X                               |                  |                  |                     |                  |                     |                  |                             |
| Randomization 1 (facility- vs. workplace-based)             |                                 | X                |                  |                     |                  |                     |                  |                             |

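### Champion allocation is listed before the first dose that defines its analysis set, and the protocol gives conflicting times for bar allocation with no concealment during recruitment

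*Protocol*

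**What the plan says.** **Champion allocation (Randomization 2).** The Visit 0 list in section 7.3.2 gives study consent, the eligibility check, "Division into the two study randomization groups 1 and 2", the observed first dose with a month's supply, counselling and, last, "Conduct baseline questionnaire". Section 10.5 restricts the secondary-endpoint analyses to randomized women who initiated. Section 10.5.3 repeats this for the refill endpoint, which is compared by Champion status as well as by delivery arm. Section 4.1 adds a separate Champion consent, "Those who are willing to participate will sign an additional consent form", without saying when it is signed.

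**Bar allocation (Randomization 1).** Section 9.4.1 states "First, bars will be randomized at screening into either workplace-based or facility-based PrEP initiation and follow-up". In the 7.3.6 schedule the row beginning "Randomization 1 (facility- vs. workplace-based" is marked at Baseline Visit 0 and not at the Recruitment and Screening visit. The Visit 0 bullet quoted above also covers group 1. Sections 10.5 and 10.5.2 describe the ITT set as women who were screened, found eligible and randomized.

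**Recruitment and masking.** Under 5.3 the study team lists the barmaids with the on-duty manager and invites all of them. Screening consent and questionnaire follow (7.3.1). Many exclusions in 5.2 rest on self-report, such as flu-like symptoms, bone problems and current medicines. For workplace bars, 4.1 describes the site as one "where they will be recruited to the study by Community based HIV care providers". Section 9.4.1 says the trial is not blinded.

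**The concern.** Randomization protects a comparison only for the set of women fixed before the allocation is known.

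The Champion comparison is randomized woman by woman. If a woman can learn her Champion group and then take or not take the first pill, keeping only those who took it makes the compared groups depend on a post-allocation choice. The refill and adherence comparisons for secondary objective 1 would then no longer rest on randomization alone.

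The delivery comparison is randomized by bar. If the arm is known while women are listed, consented and questioned about exclusions, the mix of women counted as eligible can differ by arm even though bars were assigned at random. Primary endpoint 1 is a proportion with those women as its denominator, so any such difference enters the estimate directly. Analysis cannot reliably repair it, because women who were never listed or consented leave no data.

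**Working it through.** **1. Champion order against analysis set.** Let R be the women allocated in Randomization 2 and I the women who took the observed first dose.
- Order as listed in 7.3.2: allocation, then dose. I is a subset of R, formed after allocation is known. The analysis uses I.
- Dose first, then allocation revealed: R = I by construction, and no post-allocation selection on initiation is possible.

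The documents do not say how many women would fall between allocation and first dose (the 40-per-cell table in 9.4.1 counts women expected to join), so no size can be given for the first case.

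**2. Bar allocation, places side by side.**

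| Section | When the bar's arm is set |
|---|---|
| 9.4.1 | at screening |
| 7.3.2 | Visit 0, after study consent and eligibility check |
| 7.3.6 | Baseline Visit 0, not the screening visit |
| 10.5, 10.5.2 | after eligibility |

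These do not describe one order, and none adds a concealment step.

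**3. Background check on the planning figures.** Inputs from 9.3: 800 facility and 320 workplace women, 8.25 women per bar, cluster-size CV 0.24, two-sided alpha 0.05. Design effect DE = 1 + ((1 + CV²) × 8.25 − 1) × ICC, where (1 + 0.0576) × 8.25 = 8.725. For 10% against 25% at ICC 0.09, DE = 1 + 7.725 × 0.09 = 1.695 and power is 0.996, against 0.997 stated. Reordering the steps changes no power or sample-size figure.

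**4. Illustration of the bar-level risk.** The selection fractions are assumptions, not document figures.
- At the planned 25% workplace rate, leaving out 10% of listed women, all of them non-initiators, gives 0.25/0.90 = 27.8%. That is +2.8 points, or 2.8/15 = 19% of the 15-point target difference. Leaving out 10% of the non-initiators only gives 0.25/(0.25 + 0.75 × 0.90) = 27.0%, or +2.0 points.
- With no true difference (10% in both arms) and a share s of workplace non-initiators left out, the apparent workplace rate is 0.10/(0.10 + 0.90 × (1 − s)). The false-positive chance in favour of workplace delivery uses the same normal approximation, with 800 facility women, 320 × (0.10 + 0.90 × (1 − s)) workplace women, and DE = 1 + 7.725 × 0.02 = 1.155 at ICC 0.02:

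| s | Workplace women left | Apparent rate | Chance of a false finding for workplace (nominal 2.5%) |
|---|---|---|---|
| 10% | 291 | 11.0% | about 7% |
| 20% | 262 | 12.2% | about 16% |
| 30% | 234 | 13.7% | about 33% |

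With the arm sizes exchanged, as the 2:5 facility-to-workplace wording in 9.4.1 implies, the chances are about 6%, 15% and 32%.

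**The case against.** **The Visit 0 bullets may not be a strict sequence**, and section 4.1 speaks of randomizing enrolled PrEP clients, which suggests women already on PrEP. This is fair, but enrolment is not defined as having taken the first pill, and no other section supplies an order.

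**Recruitment leaves little discretion.** All barmaids are listed and all are invited (5.3), the research team makes the approach (4.1), and HIV, hepatitis B and creatinine results are objective. This limits selection. It does not protect the completeness of the list, the decision to consent, or the self-reported exclusions.

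Four stronger readings are tempting, and the documents do not support them.
- *Bars are allocated before their women are listed.* Section 9.4.1 says only that it happens at screening, and four other places put it later. What stands is the contradiction and the missing concealment.
- *Champion allocation precedes its consent.* Section 4.1 gives no time for the extra form, and main study consent comes first in 7.3.2. Exploratory endpoint 11 counts women "declining being part of the omni-channel PrEP Champions intervention at baseline and at each study visit", but among those who initiated, and no section removes decliners from the analysis.
- *Partner and condom reports are no longer baseline.* The Visit 0 questionnaire is listed last, although 7.1.1 speaks of patient-reported outcomes "in addition to the collection of baseline data prior to enrolment". However, 4.2 describes a baseline survey of all potential participants that covers sexual and reproductive health, and 7.3.1 has a screening questionnaire.
- *Champion status biases primary endpoint 1.* Champion allocation is individual and independent of delivery arm, so any effect on initiation should balance between arms.

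**Conclusion.** Two points hold.

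(a) Followed as listed, Visit 0 puts Champion allocation before the event that defines the Champion analysis set. In an open trial this permits selection after known allocation. The size cannot be derived from the documents; revealing allocation after the dose reduces it to zero. This is the firmer point, and it assumes only that the 7.3.2 list is followed in its order.

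(b) The time of bar allocation is contradictory, and nothing conceals the arm during recruitment. Under the screening-time reading, primary endpoint 1 is exposed to a different mix of eligible women by arm. The shifts of about 1 to 4 points and the false-positive chances of about 7% to 33% are illustrations. They assume selection in the workplace arm only, confined to non-initiators, at assumed fractions of 10% to 30% and ICC 0.02. Under the reading that places allocation after eligibility, most of this exposure disappears, provided the arm is also unknown until then.

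Neither point shows that bias will occur. Both should be settled in the text before enrolment, because analysis cannot reliably undo them.

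**What to change.** **Randomization 2.** In 7.3.2, 7.3.6 and 9.4.1, state the Visit 0 order as study consent together with any Champion consent, baseline questionnaire, observed first dose, then disclosure of the Champion allocation. The initiator set then equals the set randomized to Champion or control.

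**Randomization 1.** Bring 7.3.2, 7.3.6, 9.4.1, 10.5 and 10.5.2 to one order. Complete the bar's list first. Then complete each woman's screening consent, questionnaire and self-reported eligibility. Only then disclose the bar's arm and offer PrEP. One way is to screen a bar's listed women in a single session before opening its sealed or tablet-held allocation.

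**Cost.** Protocol wording and an allocation-release step, with no change to sample size. Staff must arrive prepared for either arm. Screening takes 1.5 to 2 hours per woman (7.3.1), so a bar of 8.25 women needs 8.25 × 1.5 = 12.4 to 8.25 × 2 = 16.5 woman-hours. A single session therefore needs several staff working in parallel. Women screened early may still wait for the offer, which matters because the workplace arm is meant to test an immediate one (4.1), so the wait should be kept short.
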